## Synopsis of Study

|                                        |                                                                                                                                                                                                                                                                                                                                                                                                                               |
|----------------------------------------|-------------------------------------------------------------------------------------------------------------------------------------------------------------------------------------------------------------------------------------------------------------------------------------------------------------------------------------------------------------------------------------------------------------------------------|
| Study Title                            | Technological visual training in Parkinson's disease: A pilot randomised parallel group trial.                                                                                                                                                                                                                                                                                                                         |
| Internal ref. no. (or short title)     | Visual training in Parkinson's.                                                                                                                                                                                                                                                                                                                                                                                               |
| IRAS Number                            | 287526                                                                                                                                                                                                                                                                                                                                                                                                                        |
| Study Design                           | A 4-week, single-site, parallel-group, RCT pilot involving human participants with a 1:1 allocation to either technological visual training or standard care group.                                                                                                                                                                                                                                                           |
| Study Participants                     | 40 people with Parkinson's disease
- Hoehn & Yahr stage I-III                                                                                                                                                                                                                                                                                                                                                              |
| Planned Size of Sample (if applicable) | 40                                                                                                                                                                                                                                                                                                                                                                                                                            |
| Follow up duration (if applicable)     | N/A                                                                                                                                                                                                                                                                                                                                                                                                                           |
| Planned Study Period                   | May 2021-June 2023                                                                                                                                                                                                                                                                                                                                                                                                            |
| Research Question/Aim(s)               | Aim I : Assess the feasibility of a technological visual training (TVT) intervention that requires wearing stroboscopic glasses and use of a tablet application in Parkinson's.
Aim II : Measure the potential effects of TVT on visual function in Parkinson's to determine if it produces greater benefit than a standard care intervention and assess the feasibility of a future large full-scale study. |

## FUNDING AND SUPPORT IN KIND

| FUNDER                                                            | FINANCIAL AND NON FINANCIAL SUPPORT GIVEN                                                                                   |
|--------------------------------------------------------------------------|------------------------------------------------------------------------------------------------------------------------------------|
| Northumbria University

Senaptec, Beaverton, OR, USA | PhD studentship

£36,000 (£12,000 per year for PhD Studentship).
In kind support equipment provided. |

## INTRODUCTION

---

### LAY SUMMARY

Parkinson's disease is a common disorder that affects the brain. It can cause both movement and non-movement symptoms. Impairments of the eyes and visual system are a common non-movement symptom that affect some people with Parkinson's (PwP). Visual disturbances can interfere with reading and driving, they can impact on walking and balance, and may contribute to hallucinations.

Research has shown PwP rely heavily on their vision for day to day activities. Visual disorders combined with balance problems can increase the risk of falls, leading to decreased physical activity and reduced quality of life for PwP.

Up to 80% of PwP experience some form of visual disturbance and yet very little research has been done around the assessment and treatment of visual disorders in Parkinson's. However, there is now evidence that visual training technologies used in sporting contexts may be of benefit for PwP.

Stroboscopic visual training (SVT) is a form of training technology which is designed to improve the connections between an individual's eyes, brain, and body. Individuals wear specialised glasses with lenses that flicker between clear and opaque. Studies in athletes have shown that SVT combined with mobile training applications can improve skills such as reaction times and hand-eye co-ordination.

We would like to find out what effect visual training has on vision in Parkinson's. We will use both traditional visual training methods and state-of-the-art technology to assess and treat the visual system. We suggest that if visual training can improve aspects of eye function in PwP, it may also have the potential to impact on balance and walking.

This will be the first study of its kind to investigate the effects of SVT eyewear and visual training technology in a Parkinson's population. Understanding the effects of visual training in PwP will help clinicians and therapists improve their treatment interventions and address a symptom of Parkinson's that has historically received very little attention both from researchers and within clinical practice.

## SCIENTIFIC BACKGROUND

---

### Parkinson's disease leads to visual impairment

Visual impairment is common in Parkinson's disease, with over 80% of people with the condition reporting at least one visual symptom^1. A large population-based study of older adults by Hamedani &

Willis (2020) found that visual dysfunction is significantly more common in people with Parkinson's (PwP) than in the general population.

Visual impairments in Parkinson's are caused by abnormalities in nearly all aspects of visual function, ranging from initial targeting of gaze through head orientation and eye movements to visual processing involving both retina and higher order brain regions.

Currently, visual assessments in PwP are conducted with eye charts, expensive devices or clinical pen and paper tests, which can be time-consuming and often require clinical expertise for interpretation. Novel modern technologies have the capability to measure visual functions using a single device within a short period of time, but these have yet to be trialled in PwP. This study will combine standardised clinical tools with touch-screen visual assessment technology (Senaptec Sensory Station, see *Appendix 1*) to objectively measure visual function and visuo-motor control in PwP.

### **Visual impairments impact gait and balance**

Visual impairments are frequently associated with postural instability and gait disorders in PwP, which increase the risk of falls and lead to loss of independence and a decline in quality of life.

In addition, deficits in the ability to use proprioceptive feedback in PwP result in greater reliance on an impaired visual system to carry out motor tasks. The combination of visual-perceptual deficits and increased visual dependence has a significant impact when accompanied by primary symptoms of Parkinson's such as bradykinesia, rigidity, tremor and postural instability. These impairments reduce a person's ability to compensate and adapt to motor disturbances, which can lead to a decline in functional tasks like walking, rising from a chair, and bed mobility.

### **Visual training in Parkinson's**

There is growing interest in the assessment and training of the visual system to facilitate visuo-motor skill within sporting contexts, however relatively few studies have explored the effects of visual training (VT) within neurological populations.

Preliminary research by Zampieri et. al. (2008, 2009) suggests that eye movement exercises combined with balance training may improve gait and gaze control in PwP. More recent work has addressed eye-movement training in relation to saccade behaviour and its potential impact on motor-related Parkinson's symptoms. Despite increasing calls for further research into the area, treatment options for visual impairments in PwP remain limited to optimising dopaminergic therapy, traditional ophthalmological approaches and standard VT (e.g. eye movement training, hand-eye co-ordination, pen and paper perceptual tasks etc.).

## **Technological visual training**

Recent years have seen an increase in the use of technology in neurorehabilitation. In addition to mobile treatment apps, technological progression has led to the development of VT devices that could be deployed by clinicians or patients to improve visual function.

Stroboscopic VT (SVT) systems involve the intermittent reduction in visual input to create suboptimal visual conditions, which can be used during standard visual training tasks or combined with mobile training applications. The concept is based upon the premise that stroboscopic interruption of vision might enhance visual–motor control by reducing reliance on visual feedback and encouraging greater use of other senses. The area has seen a substantial growth since 2011 as new and improved eyewear technology has been developed and used in sports vision training.

Research performed on healthy adults, has demonstrated that SVT improves visual cognition, anticipatory and reaction timing, visual acuity, hand-eye co-ordination, visual attention and information encoding. More recent research indicates that SVT may be more effective than conventional visuomotor training for improving visuomotor abilities in athletes.

A recent study by Shalmoni & Kalron (2020) purports to be the first of its kind to investigate the use of SVT within a neurological population. They examined the immediate effect of SVT on cognitive function, gait and static balance performance in people with multiple sclerosis (MS). Their findings demonstrated that SVT enhanced information processing speed immediately after training. While these findings were based on an MS population, the authors suggest that their research could have implications for the elderly and other neurological populations.

## **Original contribution to knowledge**

Visual function is a major area of decline in Parkinson's progression. While there is emerging evidence to suggest VT may have a positive impact on visual function in clinical neurological populations, there remains a significant gap in the literature around the effect of VT in PwP.

This pilot study aims to address this gap by exploring the potential role of VT in PwP. It will assess the feasibility and potential effectiveness of a technological visual training package involving the use of a mobile application and stroboscopic glasses (see *Appendix 2*) within a Parkinson's population. To the authors' knowledge, this will be the first study of its kind to investigate the use of technological visual training (TVT) in PwP.

Before performing a large RCT (phase III study), a pilot study needs to prove the feasibility and potential effectiveness of a technological visual training intervention involving the use of a mobile application and stroboscopic glasses within a Parkinson's population.

## **Research aims**

The aims of this study are to

1. Assess the feasibility of a technological visual training (TVT) intervention that requires wearing stroboscopic glasses and use of a tablet application in PwP
2. Measure the potential effects of TVT on visual function in PwP to determine if it produces greater benefit than standard (non-technological) care and assess the feasibility of a future large full-scale study.

## **Secondary Objectives**

- i. To examine the impact of visual training on balance and gait (walking) outcomes in people with Parkinson's.
- ii. To explore other effects related to visual training including participants' health status, quality of life, self-efficacy, levels of activity and participation.
- iii. To compare visual assessment outcomes using the Senaptec Sensory Station with standardised visual assessment tools currently used in clinical practice – a potential validation study.

## **METHODS**

---

**TRIAL DESIGN:** A 4-week, single-site, parallel group, pilot RCT (allocation ration: 1:1)

### **PARTICIPANTS**

A convenience sample of community-living ambulatory older adults with mild-to-moderate Parkinson's disease ( $n=40$ ) will be equally divided and randomly assigned (via random number generator) to either Group A ( $n=20$ ) or Group B ( $n=20$ ).

### **Recruitment**

Potential participants will be recruited through Northumbria Healthcare NHS Foundations Trust (NHCFT) Parkinson's service who care for over 1000 people with Parkinson's disease and related conditions annually. PwP will be identified through attendance at the Movement Disorders Clinics at Northumbria Healthcare NHS foundation trust, for which [name] (co-investigator of this study) is the clinical lead. Investigators will attend the North Tyneside Movement Disorders clinic weekly to work clinically as honorary clinical physiotherapists. If required, it will also be possible to recruit participants from other movement disorder clinics within NHCFT (such as Blyth, Morpeth and Wansbeck), where participants live sufficiently close to Northumbria University Coach Lane campus. Research personnel will be available at clinics as required to invite participants to consider the study.

Additionally, we will recruit participants from Gateshead Health NHS trust, where PwP will be identified

through the Movement Disorder Clinics at Gateshead, which are led by [name] (Consultant Geriatrician). Verbal consent to their clinician will be required from patients in clinic for their details to be passed to the researchers. Research personnel will be available at clinics as required to invite participants to consider the study, and referrals will be made to the researchers during their attendance or via secure nhs.net email. If sufficiently interested, participants will be given a Participant Information Sheet (PIS) concerning the study. The invitation will be followed up by a telephone call during the week to assess willingness to participate. If willing, a mutually convenient time for assessment will be organised, and the invitation to attend will be extended to a carer or spouse.

If additional participants should be required, participants may also be recruited from previous Northumbria University studies where participants have consented to be contacted regarding participation in future studies, and from Parkinson's UK. Parkinson's UK will be provided with a lay summary of the study and a participant information sheet, with the contact details of the Principal investigator. Parkinson's UK will place this study on the study recruitment section of their website and newsletters to advertise the study to potential participants. Potential participants who get in touch with the principal investigator to be involved in the study will be screened for inclusion and exclusion criteria over the telephone, and if eligible for the study, a mutually convenient time for assessment will be organised, and the invitation to attend will be extended to a carer or spouse.

The study has been accepted onto the NIHR portfolio, so the DeNDRoN network will also be involved for assistance with participant recruitment as required. Participants will be identified using the DeNDRoN Research Case Register. Registrants have a confirmed diagnosis of dementia or neurodegenerative disease (including Parkinson's Disease) and have expressed their interest in hearing about local research relevant to their condition. Registrants have given their written or verbal consent for their medical notes to be accessed and screened by members of the DeNDRoN team to match them to a (NIHR portfolio) study. The register currently has several hundred PwP registered who have expressed their willingness to consider research participation, therefore it is anticipated the register will positively aid recruitment to this study if additional support is required.

Only members of the North East and N. Cumbria DeNDRoN team are permitted access to the register, therefore the initial approach will be made by them. If the patient expresses interest during the initial approach (consisting of a telephone call briefly outlining the study), with their consent, their contact details will be provided to the study team for further follow up.

The research team are confident that 40 participants can be recruited based on previous work by the Parkinson's service which has recruited similar numbers to exercise trials for 12-week exercise interventions. The study is expected to have a low attrition and a high compliance rate given that the intervention periods (4 weeks each arm) will be home-based with therapy supervision.

### **Eligibility criteria for participants**

#### ***Inclusion criteria:***

- Clinical diagnosis of Parkinson's by a movement disorder specialist according to UK brain bank criteria (H&Y stage I-III, see *Appendix 3*)
- Aged >50 years
- Able to walk and stand without support or assistance from another person
- Have adequate hearing/vision capabilities to allow participation in all aspects of study (if participant wears prescription glasses, they must be comfortable to remove these for short periods - up to 5 minutes at a time - in order to take part in activities whilst wearing strobe glasses)
- Stable medication for the previous 1 month and anticipated over a period of 6 months.

***Exclusion criteria:***

- History of epilepsy, seizures, migraines, severe motion sickness or sensitivity to light
- Psychiatric co-morbidity (e.g. major depressive disorder as determined by geriatric depression scale – GDS-15: <10, see *Appendix 4*)
- Clinical diagnosis of dementia or other severe cognitive impairment
- History of stroke, traumatic brain injury, MS or neurological disorders other than Parkinson's disease
- Acute lower back or lower extremity pain, peripheral neuropathy, rheumatic and orthopaedic diseases
- Unstable medical conditions including cardio-vascular instability in the past 6 months.
- If the participant is unable to comply with the testing protocol or currently participating in another interfering research project or undergoing any interfering therapy, they will not be recruited.
- Individuals who have *not* had opportunity to receive Covid-19 vaccine (please note, individuals may still be included in the study if they have been offered the vaccine but have declined due to personal circumstances).
- Anyone experiencing Covid-19 symptoms will be managed as per latest government guidelines.

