### **Neuropsychological Tests**

#### ***Geriatric depression scale (GDS-15) (Appendix 4)***

The short form GDS-15 which was created in 1986 by Sheikh and Yesavage will be used to evaluate subjects depression. This involves 15 questions about the mood of the subjects. Scores of 0 to 4 to be in the normal range, 5 to 9 to indicate mild depression, and 10 to 15 to indicate moderate to severe depression.

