## Appendix 4 – GDS

### Geriatric Depression Scale (short form)

**Instructions:** Circle the answer that best describes how you felt over the past week.

- |                                                                           |     |    |
|---------------------------------------------------------------------------|-----|----|
| 1. Are you basically satisfied with your life?                            | yes | no |
| 2. Have you dropped many of your activities and interests?                | yes | no |
| 3. Do you feel that your life is empty?                                   | yes | no |
| 4. Do you often get bored?                                                | yes | no |
| 5. Are you in good spirits most of the time?                              | yes | no |
| 6. Are you afraid that something bad is going to happen to you?           | yes | no |
| 7. Do you feel happy most of the time?                                    | yes | no |
| 8. Do you often feel helpless?                                            | yes | no |
| 9. Do you prefer to stay at home, rather than going out and doing things? | yes | no |
| 10. Do you feel that you have more problems with memory than most?        | yes | no |
| 11. Do you think it is wonderful to be alive now?                         | yes | no |
| 12. Do you feel worthless the way you are now?                            | yes | no |
| 13. Do you feel full of energy?                                           | yes | no |
| 14. Do you feel that your situation is hopeless?                          | yes | no |
| 15. Do you think that most people are better off than you are?            | yes | no |

**Total Score** \_\_\_\_\_

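### The GDS-15 cut-off in the depression exclusion points the wrong way: it flags normal and mild scores and leaves the moderate-to-severe band unflagged

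*Protocol*

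**What the plan says.** Under *Eligibility criteria for participants*, the list headed "Exclusion criteria" includes psychiatric co-morbidity. Its example is "major depressive disorder as determined by geriatric depression scale", followed by the cut-off "GDS-15: <10, see *Appendix 4".

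Under *Neuropsychological Tests*, the Protocol sets out how the scale is read. A total from 0 up to 4 counts as normal, and the two higher bands are given as "5 to 9 to indicate mild depression, and 10 to 15 to indicate moderate to severe depression". Higher scores therefore mean worse depression.

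Appendix 4, to which the criterion points, is headed "Geriatric Depression Scale (short form". It contains the 15 yes/no items and a line for the total. It gives no cut-off and no direction. The criterion is not restated anywhere else in the Protocol.

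**The concern.** In an exclusion list, meeting an item removes the person. A marker of major depression on a scale where high scores are bad should pick out high scores. This one picks out low scores.

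What is at stake is whether eligibility can be applied as written. Screening involves several people and routes: two NHS trusts, volunteers from earlier university studies and from Parkinson's UK who are screened by telephone against the criteria, and a disease register (*Recruitment*). The clinical evaluation is done by a physiotherapist from the research team (*Initial Screening and Clinical Assessment Protocol*).

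- A screener who follows the number turns away people with normal mood.
- A screener who follows the evident purpose enrols people who each meet a written exclusion. *Access to Data* provides for monitoring and audit, where such enrolments could be recorded as eligibility deviations.

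There may also be a smaller effect on the data. If mood influences effort and motivation ratings, fatigue scores or the timed Trail Making Test, uneven screening on mood adds variation that the planned analysis does not adjust for: the covariates under *Efficacy Analysis* are age, gender, disease duration and Hoehn and Yahr stage. That influence is an assumption; the Protocol does not assert it.

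**Working it through.** No power or error-rate formula applies. The check is to list every possible score and compare the written rule with the Protocol's bands.

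**Inputs**
- Range of the scale: 0 to 15, which is 16 possible totals (15 yes/no items, Appendix 4).
- Bands: 0 to 4 normal, 5 to 9 mild, 10 to 15 moderate to severe (*Neuropsychological Tests*, GDS-15 entry).
- Written rule: a score below 10 marks the condition to be excluded (*Exclusion criteria*).

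**Rule as written against the bands**

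| Score | Band in the Protocol | Number of scores | Flagged by the written rule? | Flagged if the sign is turned round at 10? |
|---|---|---|---|---|
| 0 to 4 | normal | 5 | yes | no |
| 5 to 9 | mild | 5 | yes | no |
| 10 to 15 | moderate to severe | 6 | no | yes |

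- Flagged as written: 5 + 5 = 10 of 16 scores, all normal or mild.
- Not flagged as written: 16 − 10 = 6 scores, exactly the moderate-to-severe band.
- With the sign turned round at the same cut-point: 6 scores flagged and 10 not flagged, so the flagged set is that same band.

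The set flagged as written is thus the exact complement of the band that the Protocol labels moderate to severe. A normal score cannot identify major depressive disorder on this scale, so the number also contradicts the sentence in which it stands.

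**Could another section resolve it?** Appendix 4 has no threshold. The GDS-15 entry gives the bands but does not link any of them to eligibility. The direction has to be inferred.

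**The case against.** The strongest reply is that the intent is plain. The excluding condition is psychiatric co-morbidity; major depressive disorder is an example of it, and the GDS figure is a qualifier inside that example. Someone with depression can be excluded on the general words whatever the number says. A trained screener would probably read the figure as the eligible range placed in the wrong list, because the literal reading requires treating a normal score as major depression.

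Much of this stands. A reader might infer that the trial would enrol only people with moderate-to-severe depression. The documents do not support that: it is true of the number taken alone, and not of the criterion as a whole. Nor can the count of 10 out of 16 scores be turned into a number of patients, since no distribution of GDS-15 scores is given. The planned 40 is the enrolment target, not a count of people affected. A reader might also see a safety failure, but the reasoning on eligibility under *Safety Considerations* concerns conditions triggered by flashing lights, such as epilepsy and migraine, and nowhere links depression to risk from the glasses.

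The reply also makes a fair point about the remedy. The criterion and the bands cite different sources, and the band from 10 to 15 is labelled moderate to severe depression, not major depressive disorder. Keeping 10 is a reasonable inference, not something that the Protocol establishes.

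What the reply does not remove is the contradiction. The number is an operative threshold, and following it gives the wrong decision. Relying on each screener to correct it silently is not a specification.

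**Conclusion.** The point holds as an internal contradiction in an eligibility rule. The numeric cut-off flags every score that the Protocol calls normal or mild and none that it calls moderate to severe, against the purpose stated in the same sentence.

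The likely consequence is inconsistent screening between readers, or participants enrolled who formally meet an exclusion. How many cannot be estimated from the Protocol. The sample size has no power calculation behind it, and no significance level or other analysis figure changes.

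The conclusion rests on two readings: that the GDS-15 entry gives the direction of the scale as the trial will use it, and that the general words of the criterion express its purpose. The suggestion that 10 is the intended cut-point rests on a further assumption, that major depressive disorder was meant to correspond to the moderate-to-severe band.

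**What to change.** Reconcile the exclusion criterion with the GDS-15 bands so that the direction of the inequality matches the purpose of excluding major depression. The Protocol's own bands point to the same cut-point with the sign turned round, so that a score of 10 or more meets the exclusion. The sponsor should confirm both the direction and the value. Any screening form in use, which was not available here, should be checked for agreement with the corrected text.

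If the cut-point stays at 10, the change is one symbol in the Protocol, plus a matching edit to a form if it carries the same wording. It needs no new procedure, visit or participant. If screening has already begun, it is also worth recording how the rule was applied, so that anyone enrolled with a score below 10 is not later treated as a deviation by default.
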